#### Participants

Employees eligible for participation in the study will be work-disabled or at risk of work disability due to medical restrictions. In order to identify these employees, we will use employer registration forms, registrations with health care organizations and insurance companies, and registration forms from those providing the intervention. Employees eligible for inclusion will be 18 to 63 years of age, perform paid labour for at least 12 h per week, and are able to communicate in Dutch. Reasons for exclusion are absenteeism for 1.5 years or longer, fulltime students with a student job, informal caregivers and/or volunteers.

In order to recruit a sufficient number of eligible employees, one or more health care providers providing an employability intervention will screen service users for inclusion in the study. When appropriate, information on the research will be provided to the patient. This will be done orally by the health care provider, possibly supported by a handout containing contact information for the researchers, what is expected of participants, privacy concerns, and so on. A self-completion card will be attached to each flyer (handout) consisting of a short checklist for inclusion and informed consent form for signing. The employee is requested to fill in the short checklist, sign the informed consent form, and send these back to the researcher. Participants will have at least 1 week to consider their participation in the study before signing the informed consent form. Participants will be screened for exclusion by the researcher on the basis of answers provided on the checklist. If an employee meets all the selection criteria and is willing to sign the consent form, randomization or matching will then place. Before the intervention starts, the first (baseline) measurement occurs. An email with a login code is sent to all participants, and they will be asked to fill in the baseline questionnaire. The questionnaire for the intervention group is identical to the one for the control group.

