#### Randomization/matching

In the case of randomization, the minimization method will be applied. Minimization aims to ensure an excellent balance for several prognostic factors in small groups [40]. Employees consenting to participate will be pre-stratified according to age (18-32 years, 33-48 years, 49-64 years), gender, and working hours (12-24 h/week, > 24 h/week). Since health care providers will treat participants in both the intervention and in the control groups, the study cannot be blinded. Matching i.e. formulating experimental and control groups on the basis of pairing participants on the basis of predetermined matching criteria will be used. These matched-criteria are age, working hours and health complaints. Thus, an employee in the intervention group will be matched to someone meeting the same criteria who will then act as a member of the control group.

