#### Timeline of the study

During recruitment, employees will be asked whether they want to participate in the research by one or more health care providers operating in the employability intervention. Participation requires employees to fill in a self-reported online questionnaire at time points T0 (baseline), T1 (6 months after admission), FU1 (12 month follow-up) and FU2 (18 month follow-up). After 18 months the study results for sustainable employability and quality of life are expected to extend into subsequent years. The timeline of the study can also be found in Figure 2.

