### Outcome assessment and data collection

The outcome assessment and data collection is identical for every employability intervention. Questions derived from different questionnaires, such as the 'National Working Conditions Survey' (NEA) [18], 'EuroQol 5 Dimensions 5 Levels' (EQ-5D-5 L) [41], 'Short Form Health Survey' (SF-36) [42], 'Trimbos/iMTA questionnaire for costs associated with psychiatric illness' (TIC-P) [43], and 'the productivity and disease questionnaire' (PRODISQ) [44], are combined into a retrospective self-reported questionnaire. The economic evaluation will be analysed from a societal perspective. This means that the most appropriate set of costs captured from the data (e.g. health care costs, productivity costs etc.), regardless of where the costs or benefits occur, will be applied [36].

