### Effect evaluation

#### Primary outcome measure

The primary outcome measure in the CASE-study is reduced sickness absence duration in calendar days. Reduced sickness absence will be measured subjectively via patient self-report records. The duration of sick leave will be calculated as the time in calendar days since reduced productivity occurred (baseline). This will then be compared with the productivity time of a person at 6, 12, and 18 months. The success of an intervention will be defined by comparing the average reduction in sickness absence between the intervention group and the control group. The employability intervention is effective when the employees in the intervention group return to work twice as quickly as employees in the control group. Data on sickness absence duration will be gathered by using the productivity and disease questionnaire (PRODISQ) [45].

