
### Sample size

For the economic evaluation of the three newly developed employability interventions, the study sample size was pre-specified by the researchers and the developers of the particular interventions. For the sample size calculation of the existing 'Best Practices', we expect that a Hazard Ratio (HR) of 2.0 indicates a relevant difference in the average number of hours/days of lost work due to work disability between employees in the intervention group and employees in the control group after 18 months. This HR is based on findings of recent studies in occupational health care [25,52-55]. With a power of 80% at a 0.05 significance level, the sample size was calculated to be 120 employees [56]. Taking into account a dropout rate of 15%, 5% per follow-up measurement time, a total of 142 participants are needed. A dropout is defined as an employee who has not filled in the questionnaire at one or more measurement time-points.

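### In the randomised evaluations, allocation comes before the self-reported baseline questionnaire, so baseline answers and baseline non-response can depend on the assigned group

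*Protocol article*

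**What the plan says.** The order of steps is in the Participants section of the protocol article. After the checklist and consent form come back, "If an employee meets all the selection criteria and is willing to sign the consent form, randomization or matching will then place". The baseline measurement follows: "Before the intervention starts, the first (baseline) measurement occurs", by e-mailed login code. The section then adds that "The questionnaire for the intervention group is identical to the one for the control group", so groups already exist when T0 is described.

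On blinding, the Randomization/matching section says: "Since health care providers will treat participants in both the intervention and in the control groups, the study cannot be blinded".

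On measurement, the Timeline section says: "Participation requires employees to fill in a self-reported online questionnaire at time points T0 (baseline), T1 (6 months after admission") and again at 12 and 18 months. According to the section on outcome assessment, items from the NEA, EQ-5D-5L, SF-36, TIC-P and PRODISQ "are combined into a retrospective self-reported questionnaire".

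Under Effectiveness in the Data analyses section, the baseline value of each outcome goes into the model to deal with regression to the mean. Sick leave in the year before inclusion, as reported at baseline, enters as a potential effect modifier. Participants are analysed in their allocated group, and wholly missing measurements are multiply imputed.

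The Sample size section says: "Taking into account a dropout rate of 15%, 5% per follow-up measurement time, a total of 142 participants are needed". It counts anyone who misses a questionnaire at any time-point as a dropout.

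**The concern.** Adjusting a randomised comparison for a baseline covariate is safe because allocation cannot have affected it. That holds when the baseline is recorded before allocation, or at least before the participant learns of it. Here T0 is tied to the start of the intervention and not to allocation. An employee who already knows the assigned group may rate health or recall past sick leave differently because of it. Adjusting for such a value, or testing effect modification by it, can then introduce bias where it was meant to remove it.

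Non-response raises a second problem. An employee who fails to complete T0 before allocation is simply not enrolled. One who fails to complete it after allocation is a missing participant in a named arm. If employees assigned to usual care are less inclined to log in, the loss differs by arm and the balance that minimisation was meant to provide is weakened. The Discussion section acknowledges selection by unblinded providers and a Hawthorne effect, but not this risk.

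**Working it through.** **1. Order of steps.** Participants section: checklist and consent, then randomisation or matching, then the T0 login. The only limit placed on T0 is the start of the intervention. No sentence in the article delays allocation, or its disclosure, until T0 is returned.

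**2. Where T0 answers are used.** For the effectiveness outcomes, T0 supplies the baseline covariate and the prior-year sick-leave effect modifier. Both are self-reported.

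**3. The plan's own sample size.** Inputs from the Sample size section: 120 employees before dropout; 15% dropout, made up of 5% at each of three follow-ups.

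- 120 / (1 − 0.15) = 141.2, rounded up to 142. The stated figure is reproduced.
- 3 × 5% = 15% is used up by the 6-, 12- and 18-month questionnaires. Nothing is left for T0, although the dropout definition includes it.

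**4. Effect of T0 loss after allocation.** The article gives no T0 non-response rate, so the rates below are assumptions. Remaining = 142 × (1 − T0 loss) × 0.85. Needed = 120 / [0.85 × (1 − T0 loss)], rounded up.

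| Assumed T0 loss | Remaining of 142 | Needed to keep 120 |
|---|---|---|
| 0% | 120.7 | 142 |
| 5% | 114.7 | 149 |
| 10% | 108.6 | 157 |
| 20% | 96.6 | 177 |

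This treats T0 loss and follow-up loss as independent. If every T0 non-responder would have missed a follow-up anyway, 120.7 still remain. If the two groups do not overlap at all, 5% leaves 142 × 0.80 = 113.6 and 10% leaves 142 × 0.75 = 106.5.

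**5. Effect on power.** The article gives HR 2.0, 80% power and a 0.05 level, but no event probability and no sidedness; two-sided is assumed.

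- Schoenfeld events: 4 × (1.960 + 0.842)² / (ln 2)² = 65.3, so 66, implying 66/120 = 55% with an event.
- Freedman events: (1.960 + 0.842)² × (3/1)² = 70.6, so 71, implying 71/120 = 59%.
- Power for d events: Φ(√d × ln 2 / 2 − 1.960), with d = remaining employees × event proportion.

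| Assumed T0 loss | Power, 66 events per 120 | Power, 71 events per 120 |
|---|---|---|
| 5% | 78.6% | 81.5% |
| 10% | 76.4% | 79.3% |
| 20% | 71.4% | 74.5% |

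With exactly 120 employees the same formula gives about 80% for 66 events and about 83% for 71.

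**6. What cannot be computed.** The shift in T0 answers and the difference in T0 response between arms. The document gives no basis for either.

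**The case against.** The strongest objection is that the mechanism is inferred. A reader might conclude that employees do know their group when they answer T0 and that the baseline data are therefore biased. The article does not say when employees are told. Its reason for not blinding concerns the providers, who treat both groups. Figure 2, the participant flow, could not be examined, so the order rests on the sequence of sentences in the text. This stands: it is an unguarded risk, not a demonstrated bias.

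A reader might also infer that baseline costs are used as a covariate. The covariate sentence belongs to the effectiveness analysis, and the economic analysis describes bootstrapped cost differences without baseline-cost adjustment. Lost earnings are taken as a change from baseline income, but that is not covariate adjustment. The point is therefore confined to the effectiveness outcomes.

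It is tempting to say that intention-to-treat fails for those without T0. That goes too far. Participants stay in their allocated group, and completely missing measurements are multiply imputed. An employee with follow-up data but no T0 is covered. Imputation has little to work with, however, for someone who never logs in, and it does nothing for a T0 answer that was given but influenced.

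The sample-size figures also have limits. The T0 losses are assumed, may overlap with follow-up loss, and ignore what censoring and imputation recover. The 120 and 142 were derived for the two Best Practice interventions; the other three had samples fixed separately, although the abstract quotes 142 per intervention.

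Finally, reordering does little for the quasi-experiments. Care is assigned there non-randomly and the referral may already be known. The article does not say how many of the five evaluations are randomised, so the reach of the main remedy is unknown.

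**Conclusion.** The point holds for the randomised evaluations. The stated order puts randomisation before a self-reported baseline in an unblinded study, with nothing to keep allocation from the employee until T0 is in. The effectiveness analysis then relies on T0 as covariate and effect modifier, and T0 non-response becomes post-allocation loss with no allowance in the sample size and only partial cover from multiple imputation.

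The numerical cost is modest. At an assumed 5% to 10% T0 loss, about 115 to 109 of the required 120 remain, and power is about 78.6% to 76.4% (66 events per 120) or 81.5% to 79.3% (71 events per 120). The more important matter is allocation-dependent reporting or non-response, whose direction and size cannot be derived. The change is worth making because it is cheap and removes the risk at source, not because harm has been shown.

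**What to change.** In the Participants section, state that minimisation is run only after the T0 questionnaire has been submitted. Age, gender and working hours can be taken from the checklist or from T0, so nothing in the article requires allocation to come first. Non-completers are then never allocated, and 142 allocated employees need no further allowance for T0.

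For the quasi-experiments, form matched pairs only from employees with a submitted T0, and record its date relative to the start of care. This keeps T0 non-responders out of the match and makes the timing checkable; it cannot remove knowledge of the referral, and the report should say so.

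If practice already withholds allocation until T0 is returned, one clarifying sentence is enough. If the order must stay, add an explicit T0 allowance (149 at an assumed 5%, 157 at 10%) and report T0 completion by arm; this covers numbers but not influenced answers.

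The cost is a short delay before allocation, whose length cannot be stated because no T0 return time is given, and some employees lost before allocation, so somewhat more must be approached.

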#### Study design

As suggested by Drummond et al. (2001), a randomized controlled trial (RCT) remains the standard design for evaluating the relative effect of candidate interventions [39]. However, due to practical reasons, randomly assessing participants to the employability intervention or care as usual is not always possible in the CASE-study. Employers and occupational physicians are legally obliged to offer sickness absence guidance, and to do so, they refer employees to one or more employability interventions. Thus, a quasi experiment, comparing employees who are allocated to an experimental intervention in a non-random manner with those non-randomly assigned to a conventional intervention is regarded as the next best study design. Unlike an RCT, a quasi experiment consists of a control group derived from a large non-equivalent population. The variables are not manipulated, and participants are selected on the basis of matched criteria with those in the non-intervention group. Randomisation is not used therefore, and participants/control members are selected on the basis of their having an equal chance of demonstrating a causal relationship between the intervention and its outcomes for the control or experimental intervention. Both quasi experiments and RCTs are acceptable for the economic evaluation of employability interventions. The anticipated flow of subject enrolment in a quasi experiment or RCT is shown graphically in Figure 2.

**Figure 2 F2:**
[figure not shown]
**Participants flow**.

#### Randomization/matching

In the case of randomization, the minimization method will be applied. Minimization aims to ensure an excellent balance for several prognostic factors in small groups [40]. Employees consenting to participate will be pre-stratified according to age (18-32 years, 33-48 years, 49-64 years), gender, and working hours (12-24 h/week, > 24 h/week). Since health care providers will treat participants in both the intervention and in the control groups, the study cannot be blinded. Matching i.e. formulating experimental and control groups on the basis of pairing participants on the basis of predetermined matching criteria will be used. These matched-criteria are age, working hours and health complaints. Thus, an employee in the intervention group will be matched to someone meeting the same criteria who will then act as a member of the control group.

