### Data analyses

#### Effectiveness

All statistical analyses, performed to distinguish differences between the control group and the intervention group, will be performed according to the intention-to-treat principle. This means that the participants will remain in the group they were allocated to at baseline. All data regarding primary and secondary outcomes will be analysed using descriptive statistics. To control for protocol deviations likely to cause bias, data will be analyzed using per-protocol analyses whereby outcomes will be compared between those participants who received at least one or a partial intervention session and the control group. With the aim of correcting for possible regression to the mean, the baseline value of the particular outcome variable will be added to the model. Days of sick leave in the year before the inclusion, measured at baseline, will be added as a potential effect-modifier.

Diagnosis and prognostic parameters can be confounders, thus the Cox regression analysis for confounders will be used to adjust for differences between control and intervention groups. If necessary, differences in baseline will be adjusted for prognostic dissimilarities. Missing data will be handled using SPSS missing value analysis on item level. Completely missing measurements will be handled using multiple imputation.

The primary dependent variable is days of absence from work. In order to estimate the number of absence days, survival analyses will be used. There are two reasons why we opted to use survival statistics. Firstly, the time to sustainable employability is unlikely to be normally distributed which will make parametric statistical analysis difficult or inappropriate. Increasing productivity can occur quite early, possibly within months, but can also, as expected in the care as usual situation, may not be prolonged or may even decrease again. Secondly, survival analysis accounts for dropout by the technique of censoring. Participants who drop out will have the same hazard of sustainable employment than those that remained in the study. The Cox Proportional hazard model will therefore be used to analyse the HR of the days of sick leave duration. Reduced sickness absence duration in calendar days will be analysed with the Kaplan Meier survival method, and the differences in absence duration between both groups will be tested with a log rank test.

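### Randomised evaluations: the factors used for minimisation are not fixed in the primary analysis, so the log-rank test is somewhat conservative and loses power if those factors are prognostic

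*Protocol article*

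**What the plan says.** Under Randomization/matching the article states: "In the case of randomization, the minimization method will be applied". Its reason is that "Minimization aims to ensure an excellent balance for several prognostic factors in small groups". The factors are then named: "Employees consenting to participate will be pre-stratified according to age (18-32 years, 33-48 years, 49-64 years), gender, and working hours". That is three age bands, gender, and two bands of working hours.

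Under Data analyses, Effectiveness, Kaplan-Meier curves describe the primary outcome and "the differences in absence duration between both groups will be tested with a log rank test". No strata are named. A Cox model is also planned for the hazard ratio. Its covariates come from four statements:

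- Confounders: "the Cox regression analysis for confounders will be used to adjust for differences between control and intervention groups" (diagnosis and prognostic parameters are named as possible confounders)
- Baseline imbalance: "If necessary, differences in baseline will be adjusted for prognostic dissimilarities" (a conditional rule)
- Baseline outcome: "the baseline value of the particular outcome variable will be added to the model" (stated without condition)
- Prior-year absence: "Days of sick leave in the year before the inclusion, measured at baseline, will be added as a potential effect-modifier" (also stated without condition)

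The first two refer to differences between the groups; the last two apply always. Nowhere does the article say that age, gender or working hours enter the test or the model because they governed allocation.

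**The concern.** The allocation method and the adjustment rule work against each other. Minimisation makes the arms alike on age, gender and working hours. A rule that adds covariates in response to group differences will therefore tend to omit these three. Two things follow if they predict return to work.

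- The ordinary log-rank variance allows for chance imbalance that the design has largely removed, so the test rejects too seldom under the null.
- Leaving prognostic factors out of a proportional hazards comparison pulls the hazard ratio towards 1, away from the 2.0 used in the Sample size section.

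Both lower power relative to what the same participants could give. An adjustment made only where needed also leaves the covariate choice until the baseline table has been seen, in a study that the article says cannot be blinded.

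**Working it through.** **Inputs from the article.** Hazard ratio 2.0, power 80%, significance level 0.05 (sidedness not stated; two-sided assumed), 120 participants before dropout and 142 after 15% dropout (Sample size). Groups of equal size (Abstract).

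**The plan's own figure.**

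- Schoenfeld events = 4(1.960 + 0.842)² / (ln 2)² = 4 × 7.849 / 0.4805 = 65.3, so 66.
- Freedman events = 7.849 × [(2 + 1)/(2 − 1)]² = 70.6, so 71.
- 120 participants therefore fit an event fraction of 66/120 = 55% or 71/120 = 59%. The article gives no event fraction, so 120 can be neither confirmed nor refuted.
- Dropout: 120/0.85 = 141.2, so 142. This reproduces.
- Power with 66 events: Φ(√66 × 0.693/2 − 1.960) = Φ(0.856) = 80.4%.

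**Simulation.** The following are assumptions, not figures from the article:

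- 120 participants and exponential times, with the censoring time set for 55% events.
- Minimisation on the three factors with an 80/20 biased coin.
- Age bands in proportions 25/40/35%, gender 50/50, hours bands 30/70%.
- The same prognostic hazard ratio for each step of each factor, and a group hazard ratio of 2.0 conditional on the factors.
- 4000 replicates under the null and 2500 under the alternative (Monte Carlo standard error about 0.3 and 0.8 points).

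The unstratified log-rank test is compared with the Wald test from a Cox model containing the three factors (2 + 1 + 1 = 4 degrees of freedom).

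| Prognostic HR per level | Log-rank type I error | Adjusted Cox type I error | Log-rank power | Adjusted Cox power | Difference in power (points) |
|---|---|---|---|---|---|
| 1.0 (not prognostic) | 5.2% | 5.4% | 79.8% | 80.0% | 0.2 |
| 1.25 | 4.5% | 5.3% | 77.6% | 79.3% | 1.7 |
| 1.5 | 4.6% | 5.3% | 76.2% | 80.3% | 4.1 |
| 2.0 | 3.0% | 5.8% | 68.5% | 81.3% | 12.8 |

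Separate simulations of the same setting agree on power:

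- With 4,800 replicates, log-rank versus adjusted power was 79.2% versus 80.5% at 1.25 (log-rank type I error 4.9%), 76% versus 81% at 1.5 and 67% versus 81% at 2.0. Adjusted type I error was 5.4-5.6%.
- With 700 replicates, an unadjusted Cox test gave 76% versus 81% at about 1.5 and 66% versus 81% at about 2.0. Its type I error was 3.1% and 2.4%.

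**How strong the scenarios are.** The extreme profiles lie four steps apart (two for age, one each for gender and hours). Their hazards therefore differ by 1.25⁴ = 2.4-fold, 1.5⁴ = 5.1-fold or 2.0⁴ = 16-fold. The article gives no prognostic strength, so none of these can be singled out.

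**The case against.** Several counter-arguments are fair.

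- **The factors may be covered.** The article calls prognostic parameters possible confounders and describes minimisation as balancing prognostic factors. Age, gender and hours could be among those parameters, and the conditional sentence on baseline dissimilarities is a separate one. This reading is possible. But the confounder sentence is itself directed at group differences, and neither sentence reaches the log-rank test.
- **A covariate list belongs in an analysis plan.** That is true of the list. What is at issue is text the article does state: an unstratified test and an imbalance-directed rule, alongside minimisation.
- **The setting may not apply.** The calculation behind 120 and a hazard ratio of 2.0 is given for the Best Practice interventions only. The new interventions' sizes were set separately, although the Abstract gives 142 per intervention. The article does not say which evaluations are randomised. The power figures are therefore illustrative.
- **The simulation is not the planned Cox model.** It has no baseline outcome value or prior-year sick leave. If these carry some of the same information, the Cox model would lose less. The log-rank comparison is unaffected.

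A reader might also infer more than the text supports:

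- *The Cox model adjusts only for group differences.* It does not: two covariates always enter.
- *The log-rank test is the primary test.* Log-rank and Cox are both named for the primary outcome and are not ranked.
- *The p-values are invalid or favour the intervention.* The error is towards caution. At 1.25 and 1.5 per level, log-rank type I error in the 4000-replicate run cannot be told apart from 5%.
- *A large loss of power is established.* It arises only with strong factors.

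**Conclusion.** The point holds as a matter of efficiency and of fixing the covariates in advance, and only for the randomised evaluations; matched comparisons are outside it. The stated analysis does not reliably include the factors that governed allocation.

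The cost is about 1-2 power points at a prognostic hazard ratio of 1.25 per level, 4-5 at 1.5, 13-15 at 2.0, and none if the factors do not predict return to work. Type I error is clearly below nominal (about 2-3%) only for strong factors.

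These sizes rest on the assumed event fraction, biased coin, factor distributions and prognostic strength. They also read the planned hazard ratio of 2.0 as conditional on the factors, which the article does not specify. If it is marginal, the gap is power left unused rather than a shortfall against the planned 80%. The evaluation stays valid without the change, but the change is nearly free and should be made.

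**What to change.** For the randomised evaluations, state that the primary test of the group effect is the Cox model that always includes age band, gender and working-hours band, whatever the observed balance, in addition to the covariates already planned. Keep the Kaplan-Meier curves as description and the log-rank test as supporting, preferably stratified by the same factors. With 3 × 2 × 2 = 12 cells and about 66 events, a stratified test averages 5.5 events per cell, which is a reason to make the Cox model primary.

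The change is one sentence. The data are already collected at allocation. It uses four degrees of freedom, and the Wald test runs very slightly above nominal at this sample size (about 5.3-5.8% in the larger simulations), so a small part of the apparent gain in power is inflated size.

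### In the quasi-experiments, matching omits absence at entry and the only named group test is an unadjusted log-rank, with no rule that the planned adjusted Cox model decides

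*Protocol article*

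**What the plan says.** **Source of controls.** Under Study design, the protocol article accepts a quasi-experiment where randomisation is impractical and says that "a quasi experiment consists of a control group derived from a large non-equivalent population".

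**Matching.** Under Randomization/matching: "These matched-criteria are age, working hours and health complaints". Neither current absence nor its duration is listed.

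**Spread of absence at entry.** Under Participants: "Employees eligible for participation in the study will be work-disabled or at risk of work disability due to medical restrictions". At the other end, "Reasons for exclusion are absenteeism for 1.5 years or longer".

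**Analysis.** Under Data analyses, Effectiveness, the article gives Kaplan-Meier curves for absence duration and says that "the differences in absence duration between both groups will be tested with a log rank test". No strata, pairs or covariates are attached to that test. The same section also plans:
- a Cox model for the hazard ratio of sick-leave duration;
- Cox regression to adjust for diagnosis and prognostic confounders, stated without condition;
- the baseline value of the outcome as a model term;
- for sick-leave history, "Days of sick leave in the year before the inclusion, measured at baseline, will be added as a potential effect-modifier";
- for remaining imbalance, "If necessary, differences in baseline will be adjusted for prognostic dissimilarities".

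The section draws no distinction between RCT and quasi-experiment and does not rank the log-rank test against the Cox result.

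**The concern.** In a non-randomised comparison, protection against confounding comes only from the matching and the adjustment. The outcome is how long people stay off work, so the absence already accrued at entry is an obvious candidate for a strong predictor of it. The entry criteria let it vary widely, and the matching leaves it free to differ between groups. A log-rank test that takes no account of it compares the case mix as well as the intervention.

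The adjusted Cox model could deal with this, but the plan does not say that it decides. If the log-rank test is significant and the adjusted hazard ratio is not, or the reverse, the choice is made after the data are seen. Listing prior-year sick-leave days only as a potential effect-modifier also leaves open whether they stay in the model as a main effect once no interaction is found.

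**Working it through.** **1. The plan's own figures.** From Sample size: hazard ratio 2.0, power 80%, significance level 0.05, 120 employees, 15% dropout, 142 in total.
- 120 / (1 - 0.15) = 141.2, rounded up to 142. This reproduces.
- Events needed (Schoenfeld, two-sided, 1:1): 4 x (1.960 + 0.842)^2 / (ln 2)^2 = 65.3, so 66. Then 66 / 120 = 55% with an event. The article does not state this share; it is used below as the value that fits its 120.

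**2. Assumptions not in the article.** No true effect; 60 per arm; short-absent employees return to work at 2 or 3 times the rate of long-absent ones; they make up 55% of one arm and 45% of the other, or 65% and 35%; two-sided 0.05.

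**3. Approximate apparent hazard ratio.** With shares p and 1 - p and rate ratio r, the ratio of the arms' average rates at the start is (p r + 1 - p) / ((1 - p) r + p).
- r = 2, 55/45: 1.55 / 1.45 = 1.07
- r = 3, 55/45: 2.10 / 1.90 = 1.11
- r = 2, 65/35: 1.65 / 1.35 = 1.22
- r = 3, 65/35: 2.30 / 1.70 = 1.35

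**4. Approximate rejection rate.** The log-rank statistic has mean of about ln(HR) x sqrt(66) / 2 = ln(HR) x 4.06. For r = 2 at 65/35 this is 0.2007 x 4.06 = 0.815. Then P(Z > 1.96 - 0.815) + P(Z < -1.96 - 0.815) = 0.126 + 0.003 = 12.9%. The other cases follow in the same way.

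| Rate ratio | Split | Approximation | Simulation, unadjusted log-rank |
|---|---|---|---|
| 2 | 55/45 | 5.8% | 5.8% |
| 3 | 55/45 | 6.9% | 7.3% |
| 2 | 65/35 | 12.9% | 12% to 15%, HR about 1.22 |
| 3 | 65/35 | 23.3% | 24% to 26%, HR about 1.38 |
| 2 or 3 | 50/50 | 5% | about 5% |

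Ranges are the spread over repeated simulations. A log-rank test stratified on prior absence rejected in about 5% of runs throughout.

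**5. A second setting.** Assume a median of 6 months to return among short-absent employees, censoring at 18 months, and long absence halving the return rate or cutting it to a third. With 40% long-absent in one arm and 60% in the other, the unadjusted test rejects in 9.5% and 16% of runs. With 30% and 70% it rejects in 26% and 49%. The stratified test stays between 4.6% and 5.8%. Events are more frequent here (about 91 and 82 of 120), so these figures are not directly comparable with the table, but the direction is the same.

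**The case against.** The strongest reply is that the plan already adjusts. A reader might infer from the matching list and the log-rank sentence that prior absence is ignored in the analysis, or that all covariate adjustment is optional. The text does not support either. The Cox adjustment for diagnosis and prognostic confounders is unconditional, the baseline outcome value is to enter the model, and the conditional wording covers only the sentence that follows. That part of the objection stands and narrows the point to which result decides and how prior absence enters.

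It does not remove the point. The one analysis named as testing the group difference is still unadjusted. The baseline value is also hard to interpret for a duration: Primary outcome measure counts days from when productivity fell but labels that moment baseline. If the clock starts at inclusion, the value is zero for everyone. If it starts earlier, prior absence is part of the outcome.

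Other replies also carry weight:
- The imbalances are assumed, and at 55/45 the inflation is slight.
- Apparent hazard ratios of 1.2 to 1.4 would not by themselves meet the article's own standard of returning twice as quickly.
- Ignoring positive correlation within pairs usually makes a test conservative, so pair handling is secondary.
- The Discussion admits possible selection bias, although admitting it does not control it.

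Four further inferences go beyond the document:
- Loss of power from an uncentred interaction term: the article does not say that such a term stays in the deciding model.
- A bootstrap of unadjusted costs and QALYs: the article is silent on baseline adjustment there, and an article may condense this.
- A need to match on gender: this is a preference, since gender can enter the Cox model.
- A need to minimise on absence: randomisation already protects the RCTs.

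**Conclusion.** The point holds for the quasi-experiments only. Followed as written, the named test can report a difference that reflects prior absence rather than the intervention, and no rule gives precedence to the adjusted result that would correct it. With no true effect and 60 per arm, the false-positive rate is about 6-7% at a 55/45 split and about 12-25% at 65/35, for return-rate ratios of 2 to 3, against about 5% when stratified on prior absence. These sizes rest on assumed imbalance, assumed rate ratios and an event share of about 55%, none of which the article gives. The direction of the bias depends on which arm has the shorter absences, so it could also hide a real effect.

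The defect lies in what the article fixes, so it is not a matter of detail left to an analysis plan. Matching takes place at enrolment, and a later analysis plan can adjust for imbalance but cannot create overlap that was not recruited.

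**What to change.** For the quasi-experiments, state that:
1. The covariate-adjusted Cox hazard ratio is the deciding analysis. Prior-year sick-leave days, or absence at inclusion, enter as a fixed main effect alongside the matching factors (age, working hours, health complaints).
2. The matched pairs are respected, by stratification or a robust variance.
3. The log-rank test is descriptive, or is stratified on prior absence.
4. Effect modification by prior sick leave is examined in a separate model.
5. Where the control pool allows, matching also uses broad classes of absence status or duration.

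Items 1 to 4 change only wording: prior-year sick leave is already measured at baseline and the Cox model is already planned. Item 5 makes matching somewhat harder. That cost is real, because four of the nine interested programmes could not take part for lack of participants or of a comparable control group. Broad classes, used only where the pool permits, keep it small, and items 1 to 4 do not depend on it.
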